**Direct benefits**

Parents will have access to child blood lead level testing, which is currently generally unavailable to most children in Kenya. Parents will also have access to interviews, messaging and home visits conducted by study staff who are trained in providing guidance on ways to avoid pediatric lead exposure.

Health facility staff will have access to training on blood lead level testing and will have practical opportunity to practice using point of care blood lead level test devices.

**Indirect benefits**

Since access to BLL testing for young children is limited in Kenya, this study with have a benefit on the societal level, given that this study may contribute to public awareness on lead as a neurotoxic substance and ways to avoid lead. The knowledge generated could have a beneficial impact on reducing lead exposures in parents and young children and may have future impact on policy and structural level changes to reduce lead exposures.

## **Informed Consent Process**

Informed consent is a process that is initiated prior to the individual agreeing to participate in the study and continues throughout study participation. Consent forms will be reviewed and approved by the ERC and IRB before use. Consent forms will be available as English and Kiswahili versions. We will only enroll participants who are able to communicate in English or Kiswahili. If the individual is illiterate, study staff will read the consent form out loud to the individual, and another staff member will be asked to witness their answers to questions regarding the consent process and their signing of the form. Parents and clinicians will provide consent for participation on behalf of themselves.

Study staff will explain the research study to the participant and answer any questions that may arise. A consent form describing in detail the study procedures and risks will be given to the participant. Extensive discussion of risks and possible benefits of study participation will be provided to participants. The participant will read (or have the form read to them) and the staff member administering consent will ask questions of the participant to assess comprehension of the study. The participant will sign the informed consent document prior to any study-related assessments or procedures.

Participants will be given the opportunity to discuss the study with their partners or think about it prior to agreeing to participate. They may withdraw consent at any time throughout the course of the study. All participants can refuse any research procedures at any time. If there is any reluctance to undergo study procedures, we will revisit consent and remind them that all participation and procedures are voluntary and ask if they wish to continue participation. If participants do not present for the in depth interview or follow up visits after 3 successful tracing contacts are made, we will consider this withdrawal from the study.

A copy of the signed informed consent document will be given to participants. The rights and welfare of parent participants will be protected by emphasizing to them that the quality of their clinical care will not be adversely affected if they decline to participate in this study. The rights and welfare of clinician participants will be protected by emphasizing to them that their clinical practice will not be adversely affected if they decline to participate in this study. The consent process will be documented in the research record.

PARTICIPANT CONFIDENTIALITY AND PRIVACY

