## **Aim 2 Sample Size and Power**

*Sample size:* 1,500 children will be enrolled and undergo POC BLL testing. We anticipate this sample size is required to achieve N = 100 with high BLL (e.g., ≥ 5 ug/dL), based on estimated of high BLL in ABC child participants at age 12 months (8.2%). Should we achieve our target of N = 100 randomized prior to enrolling 1,500 parent-child pairs, we will stop enrollment early.

Parents of these children with high BLL will be randomized to immediate messaging tailored per in-clinic survey alone vs the same protocol along with a home visit for home observational checklist + reinforced messaging per home findings (N = 50 in each arm). Follow up visits at 3 and 9 months will include surveys of message recall, behavior change to reduce exposure, and a BLL recheck.

*Power:* Primary outcomes will be recall of survey identified exposure risk factors and self-reported uptake of risk reduction behavior. Assuming 5% attrition and 10% attrition at the 3 and 9 month re-check visits, respectively, we anticipate n = 95 and n = 90 at re-check visits, respectively. Assuming n = 90, alpha = 0.05, a one-sided test, and an observed recall or uptake of ≥ 67% within an arm, we will have ≥ 80% power to exclude a recall or uptake of < 50%. For an observed recall or uptake of > 43% within an arm, we will have ≥ 80% power to exclude the possibility that recall / uptake is actually < 25%.

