Detailed contact information will be collected for each participant, including primary and secondary phone numbers, and household address (or information about location of the household). This contact information will be kept confidential and stored securely. Reminders of upcoming visits will be via phone calls and/or SMS. If a parent fails to return for scheduled follow-up visits, the study nurse will contact the participant via cell phone. If the study nurse is not able to contact the participant via cell phone, or if no telephone number is provided, study counselors will trace the participant at their household within 2 weeks of the scheduled follow-up time.

DATA MANAGEMENT

All data management activities will be co-overseen by the Seattle-based and Kenya-based data management team. Our teams have collective over 20 years of experience.

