**Exploratory outcomes will be uptake of BLL recheck and change in BLL at 3 and 9 months.**

Return for a re-check. Return for a re-check visit is an indicator of parent awareness of importance of reducing lead exposure. We will summarize the proportions of parents returning for each BLL re-check visit for each arm, and compare to our benchmark of 50%, as for primary outcomes. We hypothesize that re-check will be high for both groups, and that re-check will be higher in parents with higher child BLLs. We acknowledge this outcome may have less variability across arms and may be subject to bias, given that participants will be provided a small reimbursement at each clinic visit.

We consider BLL change to be a distal indicator of effectiveness. In Lumumba et al,*^41^* standard deviations (SDs) were 15.5 ug/dL for maternal and 1.9 ug/dL for cord BLL. We anticipate that the SDs for child BLL will be lower than for adult women but higher than for cord samples.

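### The withdrawal rule in the consent section can remove a reachable randomised parent before the 9-month visit for a missed visit or interview, without consent having been withdrawn

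*Protocol*

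**What the plan says.** Protocol, Informed Consent Process, treats non-attendance as leaving the study: "do not present for the in depth interview or follow up visits after 3 successful tracing contacts are made, we will consider this withdrawal". The same paragraph states that "All participants can refuse any research procedures at any time", and attaches no loss of study membership to such a refusal.

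Protocol, Aim 2 Follow-up Procedures: every randomised parent is scheduled for re-checks at 3 and 9 months. The knowledge, attitude and practice (KAP) questionnaire, which yields recall and uptake, is given at those two visits. A subset of 20 is invited to an in-depth interview at the 3-month visit.

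Protocol, Retention Plan: after a missed visit the nurse telephones. If that fails, "study counselors will trace the participant at their household within 2 weeks of the scheduled follow-up time".

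Protocol, Aim 2 Sample Size and Power, gives the allocation as "N = 50 in each arm". The losses allowed for are 5% at 3 months and 10% at 9 months, and the numbers expected to attend are put thus: "we anticipate n = 95 and n = 90 at re-check visits, respectively".

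Protocol, Analysis Plan, exploratory outcomes: "Return for a re-check visit is an indicator of parent awareness of importance of reducing lead exposure".

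**The concern.** The rule turns non-attendance into withdrawal from the whole study. It applies only to parents whom staff have reached three times, so it covers people who can still be contacted and who have not asked to leave. One of its two triggers is a qualitative interview that belongs to Aim 3, concerns 20 of the 100 randomised parents, and falls before the 9-month visit. Missing it has no bearing on whether the parent could give the 9-month primary outcome.

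At stake are 9-month recall, uptake and blood lead data in a trial of 50 per arm. A later analysis plan cannot recover data that staff were told not to seek. If return reflects awareness, as the Analysis Plan suggests, the parents lost may be those with poorer recall and uptake. The proportion seen among attenders would then be higher than the proportion among those randomised.

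**Working it through.** **The provisions side by side**

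- The consent section ends study participation for non-attendance at an interview or follow-up visits, once three tracing contacts have succeeded. It does not say whether one missed visit is enough.
- The same section allows refusal of any single procedure. A parent who declines the interview stays in. A parent who accepts it and does not come, despite three contacts, can be out.
- The Aim 2 follow-up section schedules both visits for all randomised parents and makes no exception for those who missed the first.
- The primary outcomes are questionnaire items. Nothing in their nature requires a clinic visit, and the Retention Plan already provides phone and household contact.

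**The plan's own figures**

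Inputs from Aim 2 Sample Size and Power: 100 randomised, 50 per arm; attrition 5% and 10%; one-sided alpha 0.05; 67% observed against 50%, and 43% against 25%.

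- Attending: 100 × 0.95 = 95 and 100 × 0.90 = 90, as stated. This is 45 per arm at 9 months.
- Power with variance at the observed rate: Φ((p1 − p0)/√(p1(1 − p1)/n) − 1.645).
- 67% v 50%, n = 45: 0.17/√(0.67 × 0.33/45) = 2.43, giving 78.2%.
- 43% v 25%, n = 45: 0.18/√(0.43 × 0.57/45) = 2.44, giving 78.6%.

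Both are within 2 points of the stated 80%. The plan's power therefore corresponds to about 45 attending parents per arm.

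**What attrition could do to the estimate**

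Take 67% among 45 attenders (0.67 × 45 = 30.15) and put it over the 50 randomised, for different assumptions about the 5 missing:

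| Missing parents | Proportion of 50 | Attenders' figure minus this |
| --- | --- | --- |
| all fail | 30.15/50 = 60.3% | 6.7 points |
| half as good (33.5%) | (30.15 + 1.675)/50 = 63.65% | 3.35 points |
| equal (67%) | 67.0% | 0 |
| all succeed | 35.15/50 = 70.3% | −3.3 points |

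If non-returners do no better than returners, the gap is 0 to 6.7 points. At 20% missing, which is an assumption and not a plan figure, it would be 0 to 13.4 points (0.67 × 0.20).

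In whole counts at the worst case, 30/45 = 66.7% has an exact one-sided p of 0.018 against 50%, while 30/50 = 60% has p = 0.101.

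**How much belongs to this rule**

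Only parents removed after a missed 3-month visit or interview, who would otherwise have given 9-month data, count. At the planned attrition, 5 of 100 miss the 3-month visit, so that route can supply at most 5 of the 10 expected to be missing at 9 months. The interview route draws on the 20 invited. The documents give no figure for non-attendance there.

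**The case against.** The strongest reply is that the rule is narrower than it may look. It needs three contacts that succeeded, so unreachable parents fall outside it. It speaks of visits in the plural. It follows a commitment to revisit consent where there is reluctance, and can be read as a limit on pressing people who have been reached repeatedly and still do not come. Aim 3 interviews have their own consent, so which study is meant is open there. Later visits are not expressly cancelled. The planned fall from 95 to 90 already leaves room for everyone missed at 3 months to stay lost, so the rule does not by itself push numbers below plan.

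These points stand as limits on the size of the problem. They do not remove it: losing the later visit is the ordinary meaning of withdrawal from a study, and if something milder is meant the text should say so.

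A reader might go further and infer three things that the documents do not support:

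- That one missed visit alone makes a parent withdrawn. The three-contact condition rules this out.
- That the primary analysis is confined to returners and so is biased upward. Attenders are the basis of the power calculation only, and discounting for attrition there is normal practice. The Analysis Plan speaks of parents within each arm, and the denominator and handling of missing answers may be in an analysis plan not shown.
- That the re-check return rate is inflated by dropping withdrawn parents. No text drops them.

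The Analysis Plan also links return to awareness, not directly to recall or behaviour, and cautions that reimbursement may affect return. Informative loss is therefore plausible rather than established.

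**Conclusion.** The point holds as a defect in a conduct rule. The consent section can end follow-up before month 9 for reachable parents who have not withdrawn consent, and it is inconsistent with the right to refuse single procedures and with the visit schedule for all randomised parents. The resulting loss of primary outcome data is avoidable and may be informative.

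The possible gap between attenders and all randomised parents is 0 to 6.7 points at the planned 10% attrition. This assumes 67% observed, 45 of 50 attending, and non-returners doing no better than returners. The upper end needs every missing parent to fail and counts all attrition, so it is a ceiling on the problem and not an estimate of this rule's effect. The change of p from 0.018 to 0.101 is the same worst case. It shows that the plan's own 67% against 50% comparison is sensitive to who is missing, not that this rule would reverse it.

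**What to change.** Amend the Informed Consent Process section so that:

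- a visit or interview still missed after three successful contacts is recorded as missed, and tracing for that visit stops;
- only an explicit withdrawal of consent ends follow-up;
- the 9-month visit is still attempted for every other randomised parent;
- the KAP questions may be asked by phone or at the household tracing contact that the Retention Plan already provides, if the parent will not come to the clinic.

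Stopping tracing for the missed visit keeps the protection against repeated pressure. The cost is a change to protocol and consent wording, approval by both ethics bodies, and a few more contacts by existing staff. Sample size and primary outcomes stay as they are.

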**Confidentiality**

To protect participant confidentiality, all key personnel will be trained in the Protection of Human Subjects before they begin working on the study. Study staff will take every precaution to protect participants’ confidentiality.

*Participant identifiers:* Name, address, phone number, birthdate, whether the participant is a parent or key informant, and child age (if a parent) will be attached to a coded study ID number. The key to this link will be stored in paper format and secured with lock and key. Only study staff will have access to this link-log. After data collection and initial data analysis are complete, we will retain the link between study code numbers and direct identifiers for the length of time required by US state and/or federal law, and Kenyan law, to maintain integrity of study data. After this period, the links to identifiable data for this cohort will be destroyed.

*All Study data* will be collected and stored on secure password-protected UW cloud-based storage, such as on UW OneDrive, on an electronic REDCap database on study tablets or laptops, or in paper under lock and key. All data will be password protected or secured with lock and key. Data will only be retrievable by study staff.

**Privacy**

The in-depth interviews/key informant interviews will occur in a neutral private location of the participants preference, which could include quiet private area in the recruitment clinic or office, at the participant’s home, on the phone, or via teleconference on a platform like zoom. Study staff will make all efforts to ensure the privacy of participants. At home visits, this will include wearing plain clothes. At clinic or office visits, a private room will be used for the interviews. If phone call or teleconference are used, the study team will ensure that both the interviewer and study participant are in quiet private areas prior to commencing.

## **Future Use of Stored Specimens and Other Identifiable Data**

Environmental media (e.g., water) samples may be used for analysis of additional contaminants in the future.

Child blood samples may be used for analysis of additional analytes (e.g., environmental contaminants, nutrients) in the future.

## **Retention Plan**

Parent participant retention procedures only apply to a subgroup of Aim 1 and a subgroup of Aim 2 participants.

Aim 1 participants are involved in the ABC study. The ABC study employs various strategies to enhance retention in the parent study, and similar approaches will be used for LEIP. Enrollees will be asked to complete an updated contact form during the enrollment visit to enable follow-up. Additionally, with participants’ permission, study staff may accompany the participant to their residence after the enrollment visit to record residence information for contact tracing. Participants are provided reminder cards and SMS messages for study clinic appointments and ABC study staff conducts active tracing for missed visits through phone calls and home visits.

In this proposal, Aim 1 participants who are screened with a blood lead test may go on to participate in an in-depth interview or a follow up home visit sub study followed by an in-depth interview. We will aim to reduce participant burden for these participants by scheduling the interview and home visit at the participant’s convenience. Incentives of 800 Kenyan shillings (~$8 USD) will be provided as reimbursement for participant time.

Aim 2 involves participant retention for children enrolled in a two arm intervention. Intervention participants will be asked to participate in two follow up visits at the clinic.

The study team has a long history of high retention of parent participants and their young children in cohorts in Nairobi. At the point of informed consent, the parents will be explained the importance of attending follow-up BLL recheck visits, and will schedule the follow-up visits at the time of testing. For these follow up blood lead test visits that occur in the clinic, all participants will receive 800 Kenyan shillings (approximately 8 US dollars) as reimbursement for travel and effort for each clinic visit. This may enhance retention. This will include the IDIs for parents for Aim 3.

Detailed contact information will be collected for each participant, including primary and secondary phone numbers, and household address (or information about location of the household). This contact information will be kept confidential and stored securely. Reminders of upcoming visits will be via phone calls and/or SMS. If a parent fails to return for scheduled follow-up visits, the study nurse will contact the participant via cell phone. If the study nurse is not able to contact the participant via cell phone, or if no telephone number is provided, study counselors will trace the participant at their household within 2 weeks of the scheduled follow-up time.

DATA MANAGEMENT

All data management activities will be co-overseen by the Seattle-based and Kenya-based data management team. Our teams have collective over 20 years of experience.

## **Types of Data**

Study participant self report data will be collected using an electronic REDCap database on study tablets or laptops [<https://www.iths.org/investigators/services/bmi/redcap/>]. Enrollment data may also be abstracted from medical records.

Audio files and field notes: In-depth and key informant interviews (IDI/KII) will be recorded on a portable audio recorder. Study staff will take field notes during or immediately after each IDI/KII. Audio files and field notes will be uploaded to a secure cloud-based password-protected server such as UW OneDrive. Once the audio files have been uploaded to the secure server, they will be deleted from the audio recorder.

Transcripts: Study staff will transcribe IDI/KII audio files and, if applicable, translate them to English. These transcripts will be stored on a secure cloud-based password-protected server such as UW OneDrive.

## **Data Entry and Cleaning**

Data will be entered into a electronic REDCap database on study tablets or laptops [<https://www.iths.org/investigators/services/bmi/redcap/>]. REDCap is HIPAA-compliant for the storage and transfer of protected health information, and uses SSL encrypted data transfer that is equivalent to the level of security used by banks. The database will be password protected. Data will only be retrievable by study staff.

## **Data Storage**

Data will be stored in the study password-protected REDCap database. Audio files, transcripts, and field notes will be stored on secure password-protected UW cloud-based storage, such as on UW OneDrive. A dedicated data team, consisting of a Nairobi data team and a Seattle-based data management and analysis team, will be responsible for the entry, management, and monitoring of study data. The Nairobi team will communicate frequently with the Seattle-based team for reporting, study monitoring, and analysis.

## **Study Records Retention**

After data collection and initial data analysis are complete, we will retain the link between study code numbers and direct identifiers for the length of time required by US state and/or federal law, and Kenyan law, to maintain integrity of study data. After this period, the links to identifiable data for this cohort will be destroyed.

ANALYSIS PLAN

**Aim 1 primary outcomes will be survey understandability and acceptability, agreement between in-clinic and at-home administered survey items and understandability and acceptability of risk reduction messages**. Qualitative analysis of understandability and acceptability. Transcripts of the interviews will be fed into the Dedoose data management tool for analysis. We will conduct a rapid analysis to summarize themes on understandability and acceptability of survey items and messages. The rapid analysis will also explore facilitators and barriers to uptake of recommended exposure reduction measures, and individual level determinants associated with uptake (e.g., empowerment, self-efficacy). Using exit interview transcripts, we will use a hybrid inductive and deductive thematic analysis approach based on our *a priori* selected CFIR constructs. Two coders will independently code transcripts, and generate a comprehensive codebook based on the CFIR constructs and conduct a thematic analysis. If new constructs emerge during our predominantly deductive coding, we will include them inductively. Agreement between in-clinic and at home surveys. Weekly field and co-investigator team meeting discussions will review any observed non-agreement between data from in-clinic and at-home surveys for refinement of this survey in Aim 2.

**Secondarily,** we will estimate the proportion of mothers (self-report on in-clinic surveys) and assessed homes with identified actionable targets, e.g., suspect household products, including cosmetics, chipped paint, potential occupational exposure, or other lead containing items observed using direct read instrumentation). We will describe the number and types of actionable targets identified for each participant. These data will enhance our adapted survey and messaging protocols for Aim 2. We will summarize descriptive statistics for standardized questionnaires on recall of identified risk factors, behavior change (e.g., proportions with recall of all or some factors vs. proportions with recall of some or no factors) and Risk, Ability and Attitude (e.g,, proportions with strong agreement vs. weak or no agreement). We will select questions with higher variability, and we will refine our questionnaires as appropriate for use in Aim 2.

**Aim 2 primary outcomes will be recall of risk reduction messages, and self-report risk reduction behavior. Exploratory outcomes will be uptake of the BLL re-check and change in BLL.** Balance between arms. We will compare baseline characteristics between randomization arms to evaluate balance of demographic and risk survey characteristics. We will use chi-square tests for dichotomous variables and rank sum tests or t-tests, as appropriate, for continuous variables.

**Recall of risk reduction messages and change in risk reduction behavior.** We will describe the proportion of parents with recall of all or most of their exposure factors identified on their surveys, within each arm and by child BLL. Similarly, we will describe proportions of parents self-reporting uptake of at least one of their risk reduction recommendations within arms and by BLL. We hypothesize that recall and behavior change will be moderate (e.g., greater than 50% in both arms), and that recall and behavior change will be highest for parents in the high BLL strata. Secondarily, we will explore potential differences in outcomes between arms, acknowledging that we will have limited ability to exclude small differences. Finally, we will describe the types of messaging recommendations taken up and not taken up by participants.

**Analysis of implementation strategy mechanisms.** We will summarize and explore differences in scores (e.g., for items using likert scales) for hypothesized individual determinants that may help explain uptake of each implementation strategy mechanism (e.g., knowledge acquisition, empowerment and self-efficacy, as well as male partner involvement and parent sex). Specific indicators will include perceived vulnerability, perceived risk, attitude regarding cost of lead exposure reduction, and perceived ability to take up messages). We hypothesize that parents with uptake of risk reduction behavior will have higher perceived vulnerability and risk, and greater perceived ability to take up messages compared with parents with lower uptake.

We anticipate that scores for individual determinants assessed using our questionnaires will be non-normally distributed and we will explore the relation between these cofactors (e.g., Risk, Attitude and Ability) and uptake of exposure reduction measures using non-parametric tests. We will use Wilcoxon rank-sum tests and log binomial regression or modified Poisson regression with robust errors, as appropriate to explore the relation between Risk, Attitude and Ability scores and uptake of risk reduction messages.

